## Comparison of the cardio-respiratory values in response to EMS against the maximum physiological values recorded during the fitness test.

## Change in muscular function after the EMS session

## Change in plasma protein content after the EMS session

**Analysis of the results**

Using simple and multiple regressions, the relationship between the different variables will be analysed with the aims to:

**Objective #1**

Identify correlations between ∆Intensity (V3-V2) and the cardio-respiratory response to EMS (raw values and % of maximum values)

**Objective #2**

Identify correlations between ∆Intensity (V3-V2) and the pain perceived during the initial session V2 (VAS reading for the intensity reached during V2) and between ∆I (V3-V2) and the change in pain perceived between V2 and V3 (VAS reading at equal intensity)

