Nevertheless, our experience (ESTIM protocol, CER #20105) shows that some patients experience difficulties in increasing the intensity of stimulation, even after several weeks of training thus limiting the treatment’s effect [17]. However, the cardio-respiratory response of a COPD patient during a session of electrical muscle stimulation has never been described. Theurel’s study, carried out with healthy subjects, suggests that minute ventilation increases significantly more when the intensity of the electric stimulation is increased than during voluntary exercise of equal intensity. Minute ventilation may increase to 10L/min (23 ± 4 vs 13 ± 3 L/min at rest) when the intensity reaches 50% of the maximal voluntary contraction [18]. Furthermore, this study shows that oxygen consumption and heart rate increase with time and intensity during a session of electrical muscle stimulation. These factors could limit the ability for patients to tolerate electrical muscle stimulation in the same way as a decrease in oxygen saturation, and are worth investigating. What is more, the abilities to produce and to tolerate muscular contraction at a given stimulation intensity vary greatly for one individual and between individuals [19, 20] particularly for thinner individuals [14]. Body composition, especially at the site of stimulation, could influence the transmission of the electric stimulation and therefore could be partly responsible for intolerance to electrical muscle stimulation. Finally, there is currently no data concerning induced muscular fatigue and the metabolic expenditure associated with a complete session of electrical muscle stimulation in COPD patients. This type of information could help determine the minimum delay to respect between two sessions of electrical muscle stimulation in order to allow optimal muscular recovery in patients and improve long-term tolerance to a course of electrical muscle stimulation.

We therefore propose to evaluate COPD patient tolerance to electrical muscle stimulation together with the cardio-respiratory response, the symptoms linked to exercise (daily exercise, maximal exercise) and felt during the electrical muscle stimulation itself (pain perception), body composition, and the muscle fatigue which follows a stimulation session.

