**Specific hypotheses:**

A large increase in ventilation, an acceleration in heart rate and/or a fall in arterial oxygen saturation during electrical muscle stimulation decreases patient tolerance to EMS.

Excessive pain perception lowers tolerance to electrical muscle stimulation. Pain perception diminishes over the course of several EMS sessions when electrical muscle stimulation is applied progressively.

Low body fat around the quadriceps is associated with increased pain perception during a session of electrical muscle stimulation and is therefore associated with lower tolerance to this training modality.

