**V2: Autonomous use of EMS, measure of pain perceived and of muscle fatigue**

The aim of this visit is to ensure that the patient can carry out electrical muscle stimulation in autonomy so that he will be able to use the apparatus at home. A full stimulation session will be carried out during which the patient will progressively take charge of the session. During electrical muscle stimulation, symptoms will be monitored (pain perception). The strength of the quadriceps will be tested before and after the session in order to measure the muscular fatigue caused by an initial EMS session. Finally, body composition will be determined during the course of this visit.

**V3: Assessment of EMS progression. Measure of pain perceived and of muscle fatigue at EMS intensity used during the sessions at home.**

The aim of this visit is to measure the pain perceived during a session of electrical muscle stimulation carried out at the EMS intensity that was used during the sessions at home. At the start of the session, the intensity of the stimulation applied will be that reached during visit 2, in order to compare the pain perceived for a given intensity, after 7 days of using the apparatus. Next, the patient will be asked to increase the intensity up to the level reached at home in order for us to calculate the intensity increase delta between V2 and V3. Throughout the course of this EMS session, the cardio-respiratory response will be measured using a portable “metabograph” fitted with a telemetric system (Oxycon mobile, Viasys). Furthermore, a blood sample will be taken before and after the session in order to measure systemic inflammation and oxidative stress levels. Lastly, muscular strength will be measured in order to determine the fatigue induced by this session.

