**Details of the electrical muscle stimulation sessions**

General concept: Simultaneous muscular stimulation of both legs induced by an electric current conducted by two cutaneous electrodes. Throughout the session, a period of muscular contraction alternates with an “active” recovery period (stimulation frequency which favours local blood circulation). The stimulation intensity is progressively increased provided it is well tolerated by the patient.

Site: LAVAL hospital and at the patient’s home

**Visit 1: Initiation session:** presentation of the electrical muscle stimulation program, positioning of the electrodes and learning how to use the apparatus.

**Visit 2: Session to gain autonomy of use:** observation that the patient can satisfactorily carry out an EMS session autonomously.

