**At home: five EMS sessions carried out autonomously at home**

During the seven days separating visits V2 and V3, the patient will be required to carry out 5 sessions at home. He will be asked to increase the EMS intensity as much as he can throughout one session and from one session to another, whilst staying beneath his pain threshold. In other words, he will have to increase the intensity frequently in order to always be at the maximum bearable intensity. For each session, the patient will have to write down the initial and final intensities along with the level of pain perceived for each. Throughout the week, we will maintain contact by phone (one initial phone call the day of the first session at home and then according to the patient’s needs) in order to answer any questions and/or solve any potential technical difficulties.

**Visit 3: Training session,** session as carried out by the patient at home.

Electrode placement

**Three electrodes on each leg:** two electrodes (50*50 mm) are placed on the skin by the lateral and the medial vastus of the quadriceps + one electrode (50*90 mm, double outlet) placed horizontally towards the top of the thigh, beneath the groin.

**
[figure not shown]

[figure not shown]
**

*Electrode placement for thigh rehabilitation*

*In this picture, the electrodes placed at the upper thigh are smaller models which will be replaced by electrodes of larger calibre, positioned side by side lengthwise (59*90 mm)*

**Electrode placement will be standardised** so as to lie by the lateral and the medial vastus motor points. The motor points will be identified for each patient individually, using a **pen electrode** that helps determine motor pathways and points of emergence.

Program

**Intermittent frequencies**: contraction at 50 Hz / “active” muscle relaxation at 5 Hz

- - - contraction 7 sec / relaxation 10 sec

**Time to reach contraction**: 3 seconds / time to relaxation: 1 second. Considering that the contraction is incomplete during the first two seconds of the contraction process, the cycles are 30%.

**Pulse width** = 400 µm

**The intensity** at which the patient begins to feel contraction of his thigh muscle is defined as the initial intensity; it is then progressively increased in order to reach the maximal bearable intensity.

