**Criteria used for analysis**

- Tolerance to EMS: pain perceived for a given stimulation intensity and the increase in intensity between sessions V2 and V3, ie. ∆Intensity (V3-V2)

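### Objective 2's V2 pain reading is taken at each patient's self-limited intensity, so on its own it mixes pain sensitivity with accepted pain and weakly tests whether pain lowers tolerance

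*Protocol*

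**What the plan says.** Protocol, Analysis of the results, Objective #2 names two pain predictors of ∆Intensity (V3-V2). One is the "VAS reading for the intensity reached during V2". The other is the change in pain from V2 to V3, as a "VAS reading at equal intensity". The section introduces all objectives as simple and multiple regressions, but Objective #2 does not name V2 intensity as a covariate.

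The general concept under Details of the electrical muscle stimulation sessions says: "The stimulation intensity is progressively increased provided it is well tolerated by the patient". The Program part starts from the intensity at which the patient begins to feel a contraction and continues: "it is then progressively increased in order to reach the maximal bearable intensity". The V2 description says: "A full stimulation session will be carried out during which the patient will progressively take charge of the session". No VAS stopping value and no common intensity are given for V2.

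The hypothesis to be tested (Specific hypotheses) is: "Excessive pain perception lowers tolerance to electrical muscle stimulation". The Introduction expects the ability to "tolerate muscular contraction at a given stimulation intensity vary greatly for one individual and between individuals".

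**The concern.** The predictor is read at an endpoint that each patient sets by his own tolerance. Where pain sets that endpoint, sensitivity shows up mainly in the intensity reached, and the VAS shows the pain the patient was willing to accept. Using the VAS without the intensity discards the half of the pair that carries most of the information on sensitivity.

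At stake is the reading of the first Objective 2 result. A correlation near zero could be reported as evidence that pain does not limit tolerance, although tolerance had already set the intensity at which pain was measured. If willingness to accept pain also drives the later increase in intensity, the sign could even run against the hypothesis.

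**Working it through.** **Inputs from the protocol.** The sample is 3 groups of 7, so 3 × 7 = 21, which agrees with the stated total. No alpha, power, effect size or SD is given. With an assumed two-sided 5% test, 80% power and Fisher's z, the smallest detectable correlation is tanh[(1.960 + 0.842)/√(21 − 3)] = 0.58.

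**Assumed model (none of this is in the protocol).** VAS = sensitivity × intensity. Sensitivity is log-normal with log-SD 0.4. Accepted VAS has mean 5 and SD 0.5, 1 or 2. VAS noise has SD 0.5. Each patient stops at the smaller of accepted VAS / sensitivity and a cap that stands for stopping without a pain reason.

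**Two patients.** Both accept a VAS of 5. One feels 5 VAS units per unit of intensity and stops at 5/5 = 1.0. The other feels 10 and stops at 5/10 = 0.5. Their sensitivities differ twofold, yet both VAS readings are 5.

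**Rank correlation of the V2 VAS at stop with sensitivity**

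| Share stopped by pain | Accepted pain independent of sensitivity | Accepted pain correlated −0.3 to 0.3 with sensitivity |
|---|---|---|
| All | 0.00 | −0.27 to 0.28 |
| About 80% | 0.23 to 0.26 | 0.02 to 0.42 |
| About half | 0.51 to 0.71 | 0.36 to 0.76 |
| About 10 to 25% | 0.74 to 0.90 | 0.65 to 0.91 |

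With all patients pain-limited and accepted pain independent, the SD of the VAS at stop is 0.71, 1.12 or 2.02. The reading can thus vary widely and still say nothing about sensitivity.

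**Alternatives, all patients pain-limited and accepted pain independent**

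- VAS and V2 intensity jointly: rank correlation with sensitivity 0.93 to 0.98.
- VAS at one common level, set at 0.6 of the median pain-limited intensity: 0.91 if everyone gives a reading, 0.88 among those who reach that level. In this model 11 to 22% stop below it, that is 0.11 × 21 = 2.3 to 0.22 × 21 = 4.6 patients, and they tend to be the more sensitive ones.

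**Consequence for the test.** Suppose the true correlation of sensitivity with ∆Intensity is −0.5, and the VAS relates to ∆Intensity only through sensitivity. Then the observed correlation is roughly −0.5 × (correlation of the reading with sensitivity). Power is for n = 21, two-sided 5%, Fisher's z:

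- reading 0.00: observed 0.00, power 5%
- reading 0.25: observed −0.125, power 8%
- reading 0.51: observed −0.255, power 20%
- reading 0.71: observed −0.355, power 35%
- reading 0.91: observed −0.455, power 55%

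**Choice of outcome.** If V3 intensity = a + b × VAS + c × V2 intensity, then ∆Intensity = a + b × VAS + (c − 1) × V2 intensity. The VAS coefficient b is the same in both models, so either outcome can be used once V2 intensity is a covariate.

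**The case against.** Several points count against a stronger reading.

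- A reader might infer that titration holds the VAS near one value for everyone, so that it cannot rank patients. The protocol does not support this. It sets no VAS stopping value, maximal bearable is subjective, and accepted pain may differ widely. The problem is what the reading means, not necessarily a loss of spread.
- A reader might also infer that every session is pushed to the limit of pain. The Program line is general, but the explicit instruction to stay at the maximum is written for the home sessions, and V2 is partly a learning session. If many patients stop for other reasons, the VAS keeps useful information.
- A reader might see a contradiction with the tolerance criterion of "pain perceived for a given stimulation intensity". The V3 description uses the same idea for a comparison within a patient after 7 days, and the second Objective 2 correlation carries that out. There is no contradiction.
- It might be thought that adjusting for V2 intensity cannot help. It can: the pair recovers sensitivity, and the planned multiple regressions leave room for it.
- The hypothesis speaks of pain perception, not sensitivity, and pain at the end of V2 may legitimately show how much headroom remains. This stands as a reason to keep the reading as a description of the stopping point. It does not make the unadjusted correlation a good test of the hypothesis.

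**Conclusion.** The point holds in a limited form. Objective #2 fixes a V2 pain predictor that, taken alone, confounds pain sensitivity with accepted pain, and it does so to the extent that patients are pain-limited at V2. The resulting correlation is then a weak test of the stated hypothesis, and a null result should not be read as showing that pain does not limit tolerance.

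The size cannot be fixed from the protocol. Under the assumed model, the reading's rank correlation with sensitivity runs from about 0 (all pain-limited, accepted pain independent) to 0.5 or more (about half stopping for other reasons, same independence). It can be as low as 0.36 in that second case if more sensitive patients also accept less pain. Only the first of the two Objective 2 correlations is affected in this way.

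**What to change.** 1. In Objective #2, replace the simple correlation with a multiple regression of V3 intensity (or equivalently ∆Intensity) on the V2 VAS, with V2 intensity as a covariate.
2. At V2, record one further VAS at a stimulation level common to all patients and passed on the way up, without changing the titration. Make it the main V2 pain predictor. The level must be the same for everyone. A level set relative to each patient's own initial intensity does not qualify, because that intensity is individual.
3. Keep the VAS at the reached intensity as a description of the stopping point.
4. Do not use a VAS/intensity ratio or slope as the predictor. It divides by V2 intensity while ∆Intensity subtracts it. With no true effect, and assuming 10 to 30% session-to-session variation in intensity at unchanged VAS, this coupling alone gives a correlation of about +0.11 to +0.28, opposite to the hypothesis.

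The cost is one extra VAS reading in a supervised session, one extra model term at n = 21, and a missing reference reading for any patient who stops below the common level. Such patients tend to be the more sensitive ones, so they should not simply be dropped; the regression in step 1 includes them. In that regression, VAS and V2 intensity should be read together, because under the model it is the pair that recovers sensitivity. In the all-pain-limited, independent case, the VAS given V2 intensity has a partial correlation of only 0.42 to 0.75 with log sensitivity. That is why the common-level reading is the better main predictor.

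### Objective 2 relates ∆Intensity to a pain change measured from the same single V2 session, so where V2 intensity is pain-limited, day-to-day variation alone can produce a negative correlation

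*Protocol*

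**What the plan says.** Under the heading Criteria used for analysis, tolerance includes "the increase in intensity between sessions V2 and V3, ie. ∆Intensity (V3-V2"). Objective #2 in the Analysis of the results correlates this quantity with pain at V2 and also with "the change in pain perceived between V2 and V3 (VAS reading at equal intensity").

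The description of V3 in the Study schedule fixes both ends of these differences. At the start of V3, "the intensity of the stimulation applied will be that reached during visit 2", so the pain change is read at the V2 intensity. As the next step, the patient should "increase the intensity up to the level reached at home in order for us to calculate the intensity increase delta between V2 and V3".

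The general Program text, in the details of the stimulation sessions, says of the intensity that "it is then progressively increased in order to reach the maximal bearable intensity". For each of the five home sessions, "the patient will have to write down the initial and final intensities along with the level of pain perceived for each". The analysis method is simple and multiple regression. The protocol plans no second V2-type baseline, and it adds no caveat about the shared one.

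**The concern.** Both variables in this correlation subtract the same V2 session. Suppose a patient is unusually sensitive on the V2 day and raises the intensity only until it becomes unbearable. He stops lower than usual. A low V2 intensity makes ∆Intensity larger. When that low intensity is applied again at V3 on an ordinary day, it hurts less, so pain appears to have fallen. A good day at V2 does the reverse. Across patients this gives a negative correlation between pain change and ∆Intensity even if the sessions at home changed nobody's pain.

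A negative correlation is also what one would see if habituation to pain allowed patients to progress. The study could therefore report that falling pain accompanies rising tolerance when it has only re-observed variation at V2.

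**Working it through.** **The plan's own figure.** The only design figure is the sample size, 3 groups × 7 = 21, which reproduces. No alpha, SD or effect size is given. With two-sided 5% (assumed) and n = 21, the critical |r| is 0.433, so the nominal rate of significance in the negative direction is 2.5%.

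**Model.**
- Pain on a given day is b × intensity + d. Here d is that day's effect, independent between days, with SD σ. Each VAS reading adds error with SD e.
- V2 intensity is raised to a limit L: I2 = (L − d2)/b.
- The V3 level is the one reached on a home day, as the V3 description states: I3 = (L + w − dh)/b. Here w is the gain in willingness (SD ω) and dh is the home-day effect.
- The pain curve does not truly change.

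Then
- ∆I = (w − dh + d2)/b
- pain change = (d3 + e3) − (d2 + e2)

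The V2 day effect d2 enters the first with a plus sign and the second with a minus sign, so

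r = −σ² / √[(ω² + 2σ²)(2σ² + 2e²)]

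**Numbers (all SDs are assumptions, in mm on the pain scale; e = 5).**
- Weakest case, σ = 5, ω = 15: r = −25 / √[(225 + 50)(50 + 50)] = −25/165.8 = −0.15.
- Strongest case, σ = 12, ω = 5: r = −144 / √[(25 + 288)(288 + 50)] = −144/325.3 = −0.44.

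Simulating 20,000 trials of 21 patients over these ranges gives significance in the negative direction in about 10% to 54% of trials.

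**If V2 is pain-limited for only half the patients (an assumption),** the rate falls to about 5% to 18%. The upper end moves by a point or two with how the other half's V2 intensity is modelled.

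**A second parameterisation** lets true gain and true habituation vary independently with equal SD. It puts a day effect at V2 only, with no reading error. Then r = −k²/(1 + k²), where k is the day-effect SD divided by the true-change SD. The simulated two-sided false-positive rates are 5.7% at k = 0.25 (r = −0.06), 14% at k = 0.5 (r = −0.20) and 66% at k = 1 (r = −0.50).

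**What does not create the artefact.** In that second model, reading noise alone, caution alone in choosing the V2 intensity, or a V2 intensity not governed by pain each gave r = 0.00. The mechanism needs a day effect on the pain-intensity relation together with titration to the limit.

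**The diary gain.** The gain from first to last home session does not contain d2 if the first home session is independent of V2; then r = 0.00 and the two-sided error is about 5%. If the first home intensity is half anchored on the V2 level (an assumption), the gain is (w − dh5 + ½d2 + ½dh1)/b and r = −½σ² / √[(ω² + 1.5σ²)(2σ² + 2e²)]:
- σ = 5, ω = 15: −12.5 / √[(225 + 37.5)(100)] = −12.5/162.0 = −0.08.
- σ = 12, ω = 5: −72 / √[(25 + 216)(338)] = −72/285.4 = −0.25.

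The corresponding significance rate is about 5% to 20%.

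**The case against.** Most of the case on the other side limits the size of the problem, and much of it stands.

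- **Titration at V2 is inferred.** The instruction always to be at the maximum bearable level is given for the home sessions. V2 is a session to gain autonomy. The general Program line makes pain-limited titration at V2 plausible but does not state it for that visit. This is why the half-limited case is shown.
- **A reader might infer a much larger effect** by supposing that the V3 level is settled on the V3 day; r would then reach −0.88 and significance 100%. The text does not support this, because it sets the V3 level as the one reached at home.
- **A reader might infer that the day effect is known to be large,** since the Introduction says that the abilities to produce and tolerate contraction at a given intensity "vary greatly for one individual and between individuals". That sentence gives no figure and no time scale, so it makes a day effect plausible and does not size it.
- **A reader might infer that the artefact confirms a stated hypothesis.** The hypotheses say "Excessive pain perception lowers tolerance to electrical muscle stimulation" and that pain diminishes over sessions. Neither predicts a correlation between pain change and ∆Intensity. The day effect has mean zero, so it does not bias the average fall in pain.
- **The stakes are modest.** This is an observational study of 21 patients, with no alpha stated, and this is one of two correlations under one of five objectives.

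None of this removes the shared baseline, which the protocol itself fixes.

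**Conclusion.** The point holds as a limit on interpretation. One unrepeated V2 session is the baseline of both variables. Where V2 intensity is pain-limited, its day effect enters them with opposite signs. Under the assumed SDs, and with the V3 level carried over from home, r is about −0.15 to −0.44, with significance in the negative direction in about 10% to 54% of trials against a nominal 2.5%. The rate is about 5% to 18% if half the patients are pain-limited. A small day effect would leave the inflation slight, and the documents do not allow a choice within the range.

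A reader might infer that the diary gain is a clean replacement for ∆Intensity. It is not: carry-over from V2 into the first home session would keep part of the bias, and ∆Intensity (V3-V2) is the protocol's own tolerance measure. The diary gain belongs beside the stated analysis.

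**What to change.** Keep the correlation in Objective #2, but state that it is descriptive and will not be taken as evidence that pain reduction drives tolerance. Alongside it, report the correlation of the same pain change with the gain in final intensity from the first to the last home session, taken from the diary. Draw a conclusion only if the two agree.

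The cost is a few lines of analysis text; the diary data are already collected. The drawbacks should be stated with the result. The home gain is self-recorded, omits the step from V2 to the first home session, covers a shorter period than the pain change, and keeps part of the bias if the first home intensity is anchored on V2. Repeating it with a later home session as the starting point lessens the last of these, at the price of a still shorter period.
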